
**Fig. 2 Fig2:**
[figure not shown]
Draft of the Business Model of the Outpatient Clinic for Personalized Psychotherapy

### Establishment of Technical Requirements

The Outpatient Clinic for Personalized Psychotherapy's key service is a platform facilitating all SCED phases: goal selection, treatment, measures, trial design (analysis, sampling, randomization, blinding, scheduling, and reviewing), data collection, and analysis (Eslick & Sim, 2014). Frequent graphing of data and adaptability to new information are crucial (Hayes, 1981). To facilitate shared decision-making, data presentation (e.g., treatment effect size, confidence intervals, graphical trajectories, means) must avoid overinterpretation, incorporate user preferences, and maintain scientific rigor (Duan et al., 2013). Using Eslick and Sim's (2014) checklist for platform selection, we decided to use m-Path (Mestdagh et al., 2022). M-path is an easy-to-use, closed-source platform with flexible ESM protocols, varied item formats, data collection and visualization, and just-in-time interventions, ideal for personalized research in clinical settings. m-Path's flexibility and support allowed us to implement a hierarchical account structure embedding therapists', supervisors', and patients' accounts under the research team. Patient data adheres to EU General Data Protection Regulation. Although m-Path visualizes patient data well, it lacks specific features for single case designs, like various trial designs or automated visual/statistical analysis. Q&C: *How will the participant flow be organized (especially, if a randomization is used in the design?) How will data analysis and visualization be conducted?*

#### Ethical Considerations and Data Protection

For all studies of the implementation process, the ethical approval is currently being obtained by the institutional ethics committee of the Department of Psychology at the RPTU Kaiserslautern-Landau. However, using the SCED infrastructure in routine clinical care and for research purposes comes with the challenge to meet requirements of treatment-related data and research data. For example, documentation and retention obligation apply to treatment-related data, research data may have to be deleted if the patient requests it. Specific in-depth interviews of Study 1 will be used to clarify questions regarding ethical considerations and data protection. An updated ethical approval will be obtained based on the results. Q&C: *Should there be a line between treatment-related data and research data? Can patients opt-out of using the SCED infrastructure and still receive psychological treatment for their condition? How is privacy secured including data gathering, transport, storage, analyses, and presentation?*

### Study 2: Development of SCED Procedure and ESM Protocol for Routine Clinical Care

The aim of the study is (1) to develop a SCED procedure for routine clinical care, (2) to develop an ESM protocol that describes the different parameters that need to be considered such as assessment duration, frequency, and sampling scheme, and (3) to find a balance between optimal and pragmatic study settings. The ESM protocol will be reviewed in discussion groups with a minimum of six psychotherapists and six patients as the stakeholders who are mostly affected by the ESM protocol (for a justification of the sample size see Study 1). The SCED protocol, along with the outcomes of the discussion groups, will be presented to the international advisory board and to the management board of the outpatient clinic to come to a final decision.

#### SCED Procedure

We created a working version based on the Risk of Bias in N-of-1 Trials (RoBiNT) scale, a critical evaluation tool to evaluate the methodological quality of intervention studies using single-case methodology (Tate et al., 2013). We outlined the procedure for routine clinical care and research projects that could use the infrastructure of the single-case clinic in the future. For routine clinical care, we plan to use a replicated ABCDE design in which EMA data is collected after the initial appointment (phase A: baseline), during up to five diagnostic sessions (phase B: diagnostic), and during the first treatment sessions (phase C: intervention). Whenever psychotherapists alter their treatment focus or change their therapeutic strategies, they can initiate a new intervention phase (phase C’, phase C’’, etc.). This allows them to directly continuously evaluate their respective therapeutic approach. Furthermore, ESM data will be collected after treatment has ended (phase D: posttreatment) and at 6-months follow-up (phase E: follow-up). Further details can be found in Table 1.

**Table 1 Tab1:** Working version for the implementation of the single-case clinic based on the RoBiNT Scale (Study 2)

Item	RoBINT Scale	Suggestions for the implementation into routine clinical care	Possibilities for future research projects
*Internal validity subscale*			
1	Design	Replicated ABCDE Design A: baseline phase B: diagnostic phase C: intervention phase (C’, C’’, etc.) D: posttreatment phase E: follow-up phase	Replicated *randomized* designs Multiple baseline designs (concurrent and non-concurrent)
2	Randomization	No randomization due to practice-oriented focus	Randomization of treatment start per patient; randomization of treatment components (and their order)
3	Sampling behavior (all phases)	Baseline, diagnostic, posttreatment, and follow-up phase: 14 surveys per phase Intervention phase: open end	At least 5 data points per phase; patients with less than 3 data points per phase should be excluded from any statistical analysis
4	Blinding patient/psychotherapist	Blinding not possible and unethical	Blinding options are restricted in psychological treatments; in the case that interventions are compared against each other, neither patients, psychotherapists, nor supervisors should be informed about the research hypothesis
5	Blinding assessors	Blinding is not possible due to the use of mainly self-report measures; patients, psychotherapists, and supervisors are not blinded to the treatment phase	Blinding options are restricted in psychological treatments; for example, an independent statistician could be blinded to the treatment phase, although the time stamps (informative for data cleaning) will always show which data points belong to the baseline phase
6	Inter-rater reliability	Treatment progress will be monitored by the patient, psychotherapist, and supervisor; there will be no formal criterium, e.g. when to change the treatment strategy	Future studies might use additional assessment methods (e.g., video recordings, external ratings, passive sensing) that allow to assess inter-rater reliability
7	Treatment adherence	Adherence to CBT is secured by regular (video-based) supervision of psychotherapists (in training) by experienced psychotherapists (> 5 years’ work experience; completion of a specialized training for supervisors or otherwise accredited based on extensive requirements)	In future research projects, the existing infrastructure for video recordings could be used to formally check adherence via independent raters to a specific treatment protocol
*External validity and interpretation subscale*			
8	Baseline characteristics	Baseline characteristics (e.g., demographics, diagnoses, symptom severity) will be routinely assessed; during the diagnostic phase, the psychotherapist will conduct a functional analysis to develop a case conceptualization	Inclusion criteria could be chosen according to the respective research questions
9	Therapeutic setting	University-affiliated outpatient clinic in Germany (INCLUDE NAME AFTER PEER-REVIEW) in which bachelor graduates can obtain their master degree in psychotherapy and master graduates can obtain their license as psychotherapists with a special focus in CBT	Future studies could also use the SCED infrastructure to cooperate with other clinics
10	Dependent variable (target behavior)	Emotion regulation processes as a transdiagnostic mechanism; based on the functional analysis in the diagnostic phase, the psychotherapist and patients have the option to create additional individualized items to monitor the treatment progress	Dependent variables could be chosen according to the respective research questions
11	Independent variable (intervention)	The treatment starts with a diagnostic phase with a subsequent intervention phase; diagnostical tools and interventions will mainly be rooted in a CBT approach	Future studies could implement specific treatment manuals and protocols, as well as compare isolated treatment elements and interventions
12	Raw data record	Data sets for each individual patient will be recorded with an indication about which data points are missing; data will be stored while respecting data protection regulations	Future studies should strive to increase compliance of assessments (e.g., have regular compliance checks by research assistants)
13	Data analysis	Patients and psychotherapists are encouraged to look at the data collaboratively through visual inspection; psychotherapists will be encouraged to look at the data with their supervisors through visual inspection	Future research questions and their respective analytic approach should be preregistered in the OSF framework before beginning the statistical analyses
14	Replication	All patients and psychotherapists will be offered to the SCED infrastructure	One or two replications are considered good, more than three replications are considered optimal; with more and more data collected, future studies could divide a large data set into different subsets (e.g., training vs. test sample) to see whether the effect is replicated in different samples and determine cross-validation
15	Generalization	The posttreatment and follow-up phase intend to assess generalization effects; different patients will be treated by different psychotherapist and psychotherapists will be supervised by different supervisors	Generalization effect should be preferably monitored throughout treatment but the evaluation before and after treatment is also acceptable; for example, future studies could investigate whether treatment effect generalizes across skills (e.g., do skills to regulate negative emotion automatically translate in better skills to evoke and maintain positive emotions) or situations (e.g., do skills to regulate interpersonal situations automatically translate in better skills to regulation intrapersonal situations)

#### ESM Protocol

We followed systematic guidelines to consider different arguments when making methodological decisions (Janssens et al., 2018). A decision matrix was created that organizes different arguments along methodological questions (Supplemental Material, S3 Decision matrix for methodological questions, https://osf.io/54ewu). Arguments include the nature of the variable of interest, reliability and feasibility issues, as well as statistical requirements. Open methodological questions include study duration, measurement frequency, number of items, sampling scheme, instruction of items, and delay allowed to respond. The matrix was filled with typical practices or recommendations for ESM studies found in the literature (Eisele et al., 2020; Janssens et al., 2018; Wrzus & Neubauer, 2023). Based on the matrix, the research team formulated methodical suggestions for the SCED infrastructure regarding each methodological question. We decided to omit the issue of statistical requirements. Instead, future studies using the SCED infrastructure should discuss statistical requirements for the respective research question and analysis in a separate pre-registration in the Open Science Framework (https://osf.io/yex48/).

We propose to collect ESM data on 14 consecutive days during each SCED phase. We decided to not limit the study duration during the intervention phase with the aim to gather information about the extent that the daily surveys are used during treatment. Alternatively, a second (or more) 14-day assessment periods could be prompted during treatment (phase C’ or C’’ etc.). We suggest to collect one signal-contingent survey per day with the option of additional event-contingent surveys whenever the patient feels something important had happened. Each event-contingent survey will trigger a measurement burst with additional five surveys, randomly presented within the following hour. This measurement burst enables to monitor momentary mood on a microlevel. We decided to apply a semi-random sampling scheme with random beeps during an individualized time in the evening (e.g., 18-22 h). As delay allowed to respond, we suggest 60 min for the signal-contingent survey with a reminder after 30 min. For the event-contingent survey, we decided to close the survey after 30 min.

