• Adapted System Usability Scale (SUS) (Brooke, 1996; Lyon et al., 2020) to evaluate the usability of the m-path app (e.g., *‘I think I would like to use this app frequently.’*) and dashboard with the visual presentation of the ESM data (e.g., *‘I think I would like to use this dashboard frequently.*’) on a 5-point Likert Scale (1 = strongly disagree to 5 = strongly agree) • User Experience Questionnaire (UEQ-S) (Schrepp et al., 2017) to assess the subjective impression of users towards the user experience of the m-path app on a 7-point Likert scale (-3 = fully agree with negative term) to + 3 = fully agree with positive term) grouped into 6 subscales: *attractiveness, perspicuity, efficiency, dependability, stimulation, novelty*	• Patients have to rate of how burdensome (0 = neutral to 10 = disturbing) and helpful (0 = neutral to 10 = helpful) each survey is *(‘How do you rate the survey today?*’) • Response times, compliance rates, and indicators of careless responding will be retrieved from the ESM surveys • ESM data will be merged with data routinely collected at the outpatient clinic (such as clinical diagnosis, severity of symptoms, and sociodemographic data); difficulties emerging during this process will be recorded in a protocol to be able to resolve the issues for future iterations	Interview questions are intended to cover different components of the SCED infrastructure: • Initial expectations (e.g., *‘What did you expect at the beginning? Have these expectations been met?’*) • Onboarding process (e.g., *‘How can we improve the onboarding process?’*) • Practical use of the m-path app (e.g., *‘How did you get on with the m-path app?’*) • Feasibility of the ESM protocol and survey (e.g., *‘Would you change anything about the survey, including the frequency of assessment?’*) • Negative side effects (e.g., *‘Did you experience any negative side effects? How could negative side effects be reduced?’*) • Clarity of the dashboard (e.g., *‘Did you use the dashboard? What would you like to change about the dashboard?*’) • Utility for clinical practice (e.g., *‘Was the app part of the treatment/supervision? What could be changed to maximize its utility?’*)

Note. Usability measures will be administered to both patients and psychotherapists after each SCED phase; supervisors will also be invited to rate the System Usability Scale (SUS) to evaluate the dashboard (i.e., the visual presentation of the data) and conduct the semi-structural interview

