Penetration	Penetration refers to the integration of a practice within a setting	Number of patients and psychotherapists who actually use the SCED infrastructure (e.g., in terms of responding to the ESM surveys; retrieving and discussing the dashboard during treatment or supervision)	(5) ESM data (including signal- and event-contingent surveys of completed ESM surveys (i.e., the last question has been answered)) is used to derive an estimate for the penetration: • Exploration of arithmetic values (e.g., median, range, mean standard deviation) for the number of completed ESM surveys for each SCED phase, especially for the open-ended intervention phase • RoBiNT scale requires each phase to consist of at least five, but not less than three data points for the analysis of SCED data (Tate et al., 2013). We will evaluate each phase separately, with ≥ 5 data points as an acceptable criterion. For each phase, we divide the number of patients who fulfill the acceptable (≥ 5 data points) criterion by the number of participating patients (6) Indication how often patients and psychotherapists retrieved the dashboards either to prepare for treatment or discuss the dashboard during treatment on a 5-point Likert scale (1 = never to 5 = every session) after each SCED phase. Psychotherapists will also be asked to indicate how often they discussed the dashboard with their supervisors • *‘How often did you retrieve the dashboard (e.g., to prepare for treatment or discuss the dashboard during treatment)?’* • *‘How often did you discuss the dashboard together with your supervisor?’*	(5) A rate ≥ 75 is considered substantial use (6) Mean scores of > 3.5/5 on each item are considered substantial use
Implementation costs	All costs needed for an implementation effort	All monetary resources needed for the implementation of the SCED infrastructure. These costs could either be anticipated (e.g., for the m-path software) or unexpected (i.e., they only become clear in the course of implementation)	Implementation costs are also difficult to calculate because they vary substantially in the different settings (7) A list of the costs we have incurred (e.g., required working time of an employee to coordinate the single-case clinic)	

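### Burst prompts have no stated spacing and are not excluded from the five-data-point use criterion, so one event can satisfy it for a whole phase

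*Protocol article*

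**What the plan says.** The ESM Protocol section of Study 2 proposes one signal-contingent survey a day for 14 days in each phase (open-ended in the intervention phase), plus optional event surveys that the patient starts. On the burst it says: "Each event-contingent survey will trigger a measurement burst with additional five surveys, randomly presented within the following hour". The purpose given is: "This measurement burst enables to monitor momentary mood on a microlevel". No minimum gap between the five prompts is stated.

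On response windows it says "As delay allowed to respond, we suggest 60 min for the signal-contingent survey with a reminder after 30 min", followed by "For the event-contingent survey, we decided to close the survey after 30 min". The second sentence names the event survey only and does not mention the five follow-ups.

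In Study 5, Table 3, the penetration domain (measure 5) is derived from ESM data, "including signal- and event-contingent surveys of completed ESM surveys". A phase is acceptable for a patient who has at least five data points. The share of participating patients who reach this is computed phase by phase and compared with a threshold of 75 (evidently per cent) for substantial use. Compliance and retention, measures (8) and (9) in the same table, are restricted to signal-contingent surveys. Measure (5) is not.

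**The concern.** There are two separate issues.

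The first is the sampling scheme. Five prompts placed at random in one hour will often fall close together. If each may also be answered up to 30 minutes late, several can wait at the same time and be completed in one sitting. They then describe nearly the same moment, whereas the burst is meant to show a course within the hour.

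The second is the decision rule. The five-data-point criterion is meant to show that a patient used the tool enough in a phase for single-case analysis. If every burst survey counts, one event produces more than five points. A patient who answered none of the 14 daily surveys could be classed as a sufficient user of that phase on the strength of one evening. The penetration rate is one of the results by which Study 5 judges whether implementation succeeded or another strategy is needed.

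**Working it through.** **Inputs from the article.** Five follow-up prompts in 60 minutes; a 30-minute closing time, stated for the event survey; at least five data points per phase; 14 daily surveys per phase outside the intervention phase. The article gives no overlap figure to reproduce.

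**Assumptions.** The five prompts are independent and uniform over the hour (the article says only that they are random). The delay d between prompt and answer is not given, so a range is shown.

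**1. Spacing, whatever the closing rule or patient behaviour.** For five uniform points on 60 minutes, P(all four gaps exceed d) = (1 − 4d/60)^5 for d below 15.
- Two prompts less than 5 minutes apart: 1 − (1 − 20/60)^5 = 1 − (2/3)^5 = 0.868, so 87% of bursts.
- Mean smallest gap: 60/(4 × 6) = 2.5 minutes. The mean gap between neighbours is 60/6 = 10 minutes.

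**2. Permitted windows, if the 30 minutes cover the follow-ups.** Divide the hour into two halves. Five prompts put at least three into one half, so at least three windows always share some moment. All five fall within 30 minutes with probability 5 × (1/2)^4 − 4 × (1/2)^5 = 0.3125 − 0.125 = 0.1875, or 19%. In 200,000 simulated bursts the largest number of simultaneously permitted windows was three in 31%, four in 50% and five in 19%.

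**3. Overlap by actual delay.** P(any overlap) = 1 − (1 − 4d/60)^5.

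| Delay d (min) | Bursts with any overlap |
|---|---|
| 0.5 | 16% |
| 1 | 29% |
| 2 | 51% |
| 3 | 67% |
| 5 | 87% |
| 10 | 99.6% |
| 15 or more | 100% |

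**4. One prompt per 12-minute block.** In simulation, two neighbours are less than 1 minute apart in 1% of bursts, less than 2 minutes in 5%, and less than 5 minutes in 32% (against 87% unspaced). Blocks help a great deal, but without a minimum gap close pairs remain.

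**5. Counting in measure (5).** One event survey plus five follow-ups gives 1 + 5 = 6 points, against a requirement of 5. The criterion is met even if one follow-up is missed (1 + 4 = 5). The last prompt comes at most 60 minutes after the event and, with a 30-minute window, is answered at most 90 minutes after it. By daily surveys alone, the patient needs answers on 5 of 14 days. None of this depends on how the prompts are spaced.

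**6. Effect on the rate.** Let p be the share of participants who reach five points without any burst, and e the share of the others who complete at least one event with four or more of its follow-ups. The reported rate is at least p + (1 − p)e. A true p below 0.75 is carried over the threshold once e reaches (0.75 − p)/(1 − p). The article gives neither p nor e, so the size of the inflation cannot be stated in advance.

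**The case against.** A reader might infer that several burst surveys are always open together and that the burst therefore cannot track mood. The article does not support that. Thirty minutes is the longest delay allowed, and a survey answered promptly is no longer open. At a delay of 1 minute there is no overlap in about 71% of bursts, and at 2 minutes in about 49%. Prompts average 10 minutes apart, so a patient who answers promptly does supply a within-hour series. Applying the limit to the follow-ups is also a reading: the sentence names only the event survey and could describe a time-out on that form. That part of the objection stands.

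Bunched answers can also be detected. Table 2 in Study 4 states: "Response times, compliance rates, and indicators of careless responding will be retrieved from the ESM surveys". This stands in part: detection afterwards does not recover the missed moments, and no handling of bunched answers is described.

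The scheme is also a proposal. Study 2 says "The ESM protocol will be reviewed in discussion groups with a minimum of six psychotherapists and six patients", Study 4 iterates on the procedure, and the supplementary decision matrix, not shown here, may hold platform details. No outcome described for Studies 4 to 6 uses a within-burst trajectory. This limits the weight of the spacing issue, but draft status also makes this the cheapest time to settle it.

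Finally, the counting issue does not follow from overlap, and the article does not say in so many words that burst surveys count. Both are true. But measure (5) covers ESM data including event-contingent surveys and makes no exclusion, whereas measures (8) and (9) in the same table are restricted. Counting burst surveys is the plain reading.

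**Conclusion.** The point holds in two parts, and the second matters more.

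First, with uniform prompts, 87% of bursts contain two prompts less than 5 minutes apart, and the mean smallest gap is 2.5 minutes. If the 30-minute limit covers the follow-ups, their permitted windows must overlap. A within-hour mood course is therefore not ensured. That is as far as it goes: how often answers are actually bunched depends on response delays that the article does not give.

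Second, as written, one event with its burst can meet a phase's use criterion within about 60 to 90 minutes, in place of use on at least 5 of 14 days. This rests only on burst surveys counting as ESM data under measure (5), not on their spacing. It can bias the penetration rate upward and so affect the judgement of substantial use. Compliance and retention are unaffected, because they use signal-contingent surveys only.

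**What to change.** 1. In measure (5), count one event together with its burst as a single data point. Counting distinct days with at least one completed survey is an alternative, and it also prevents several events on one day from meeting the criterion.
2. Spread the burst prompts, for example one random prompt in each of five consecutive 12-minute blocks, with a minimum gap between neighbours chosen to suit the length of the burst survey.
3. State whether the 30-minute closing time covers the burst surveys.

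Closing each survey when the next one opens is not advisable: without a sufficient minimum gap, some windows would last only a few minutes or less.

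The cost is a change of app settings and a sentence or two in the ESM protocol and Table 3. The penetration rate may come out slightly lower, and prompt timing becomes slightly less random and so a little more predictable to patients.
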